### Specific study rationale

The overall rationale is to address the main objectives (see below) within a controlled trial. We have used a stepped-wedge, randomised trial design which permits observer-masked data comparisons between patients awaiting intervention with those who have undergone surgery. Contrary to most stepped-wedge trials individual patients are randomised rather than clustered. In brief (more detail below), eligible participants based on clinical evaluation and radio-physiological investigations (INVEST) will be randomised to three arms with different lengths of delay before surgery (see Additional file 2). In all arms there will be a period of 4 weeks post-eligibility to arrange the logistics of surgery (time (T)–4 weeks to T0) and ensure that patients have returned to their normal life routine after various assessments. LVMR will be performed at T0 in group I; T12 (12 weeks) in group II and T24 (24 weeks) in group III. Unavoidably, participants will be aware when surgery is undertaken: this, however, fortuitously meets the assumptions of the stepped-wedge design, i.e. no effect of treatment is expected until surgery has been performed. Efficacy outcome data will be collected at equally stepped time points (T0, 12, 24, 36 and 48 weeks).

This is, in effect, a modification of a standard, parallel-arm, wait-list control design, but with several advantages. First, a stepped-wedge design is more efficient and thus improves recruitment feasibility (the bane of nearly all surgical trials). Despite the multicentre approach of this study, the problems of recruitment cannot be underestimated. Simulation demonstrates that a parallel-arm design requires a much larger sample size than that proposed for the current study at the same power. Secondly, the trial design means that there is only a one in three chance (rather than one in two for a parallel arm) of waiting 6 months for surgery, which is more acceptable to patients.

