#### Visit 2–8 - follow-up outcome assessments

All patients will complete the standardised outcome framework (inclusive of PAC-QOL and PAC-SYM) questionnaires at T–4, T0 and 12, 24, 36, 48, 60 and 72 weeks post run-in (see Additional file 2). This ensures that 24-week and 48-week post-surgery follow-up data on the primary and secondary outcomes are collected in all patients, whilst maintaining blinding of group allocation. Thereafter, participants will leave the study and return to “routine clinical care” as determined within their local NHS institution. During the first 24 weeks post-surgery patients will be quarantined from further intervention, excepting emergency interventions (e.g. for complications).

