#### Participant withdrawal (including data collection/retention for withdrawn participants)

Individual participants will be able to drop out at any time during either the treatment or follow up. Data will be retained for intent-to-treat analysis from all participants after the point of consent and recruitment as outlined in the PIS:Withdrawal from treatment criteria (no further interventions but follow up data collected){ participants will be withdrawn from the study interventions if they develop any of the following exclusion criteria:Becomes pregnant or intends to become pregnant (only in baseline and intervention phases);Subsequently diagnosed with proven cause of secondary constipation e.g. Parkinson’s disease or bowel obstruction;Develops significant inter-current illness precluding participation;Develops acute psychological problem causing safety concern;Elective withdrawal.Loss to follow up (no further interventions or follow up data collected): participants may be withdrawn from the trial if:They become lost to follow up (LTF) after at least three failed attempts by research staff to make contact via two different methods (e.g. phone and letter);Participant choses to withdraw and does not wish to participate in follow-up data collection;Participant dies or has significant incapacity making follow-up data collection impossible.

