##### Secondary objectives

All clinical outcomes derived from the standardised outcome framework will be analysed at 0, 24, 48 and potentially 60 and 72 weeks post-operatively. Outcomes will take the form of count (change in number of symptom episodes), ordinal (patient’s global impression of success) and continuous (questionnaire scores) data. Mixed models appropriate to the outcome data types will be fitted to estimate the treatment effect, adjusting for baseline values, gender, and breakthrough medication use as a potential confounder.

All participants randomized to the three groups will be analysed according to their allocation: we would allow for +/- 2 weeks from the scheduled intervention date. Eventual deviations from this time buffer will be taken into account by a modified intention-to-treat analysis. Analysis will be performed using proprietary software (Stata, Stata Corp. TX, USA) with *p* < 0.05 taken to indicate statistical significance.

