### Specific

The protocol has been reviewed by [name], Professor of Medical Ethics and Law at QMUL. Important considerations that have informed pragmatic design include:Wait-list controlled design: a waiting list control group serves the purpose of providing an untreated comparison for the active treatment group, while at the same time allowing the wait-listed participants an opportunity to obtain the intervention at a later date. In keeping with the basic ethical tenets of this design [99], the average wait will be shorter than that for routine services. This is achieved by randomising patients to receive urgent (4 weeks) or routine intervention as opposed to all having routine status as would be normal NHS clinical care. Current waiting times at most included centres are approximately 3–6 months for surgery, whereas the mean waiting time in the study will be 3 months. Survey evidence from 100 patients indicates that for a chronic condition such as CC, patients are prepared to accept a randomization strategy that allocates them to a one in three chance of waiting up to 24 weeks for surgical treatment;Limitation of intimate examinations to one time point (not repeated if performed before recruitment);Timings of outcomes: within the standardised outcome framework, outcomes will be undertaken at fixed intervals of 12 weeks before and after the intervention to 48 weeks follow up within the stepped-wedge study and thereafter in 12-week intervals within the cohort assessments up to 72 weeks. For a period of 24 weeks of follow up post-surgery, patients will not progress to further therapies, thus preventing outcome “contamination”. This “quarantine” period from major therapy progression is required to give a reasonable clinical impression of outcome. This delay is akin to that in usual NHS care during which general supportive care will be provided while further interventions are considered. Thus, this proposed “quarantine” period to 6 months confers no disadvantage and may even represent an acceleration of treatment progression. Ethically, this is viewed as a reasonable trade-off for the commitment to the research programme;Recruitment and consent: study 3 represents one of the three studies incorporated in the NIHR-funded CapaCiTY programme. Although patients may have moved sequentially through earlier treatments (and therefore studies) during the programme course, study 3 will be consented as a distinct single entity.

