## Discussion

An individual-level stepped-wedge randomised trial serves the purpose of providing an untreated comparison for the active treatment group, while at the same time allowing the wait-listed participants an opportunity to obtain the intervention at a later date. In keeping with the basic ethical tenets of this design, the average waiting time for LVMR (12 weeks) will be shorter than that for routine services (24 weeks). We acknowledge that availability of beds may represent a major bane for this trial. However, we have attempted to overcome this by allowing a 4-week run-in post-eligibility to arrange the logistics of surgery and a 2-week tolerance interval from the scheduled intervention date.

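### The surgery window includes up to 2 weeks early while questionnaires stay at fixed weeks, so a post-operative score can stand as the last pre-surgery control score

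*Protocol article*

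**What the plan says.** All references are to the protocol article.

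- **Timing of surgery** (Specific study rationale): "LVMR will be performed at T0 in group I; T12 (12 weeks) in group II and T24 (24 weeks) in group III". The same section gives the assumption behind the design, that treatment has no effect before the operation. Trial outcomes, Primary outcome, compares patients 24 weeks after surgery with controls who have not yet had it.
- **Timing of assessments** (Visit 2–8): all patients complete "questionnaires at T–4, T0 and 12, 24, 36, 48, 60 and 72 weeks post run-in". The weeks are counted from the run-in and are the same in all groups. The section relies on this common calendar to keep group allocation masked.
- **A second description of the timing** (Ethical considerations, Specific): "outcomes will be undertaken at fixed intervals of 12 weeks before and after the intervention".
- **Window and coding** (Methods of analysis, Secondary objectives): all randomised participants are analysed by allocation, and "we would allow for +/- 2 weeks from the scheduled intervention date". The Discussion repeats "a 2-week tolerance interval from the scheduled intervention date".
- **Outside the window** (same Methods section): "Eventual deviations from this time buffer will be taken into account by a modified intention-to-treat analysis". The section on participant withdrawal says "Data will be retained for intent-to-treat analysis from all participants after the point of consent and recruitment".

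**The concern.** Each group's last untreated score falls due in the week of its own operation. The window is symmetric, so an operation at week 22 in group III is on schedule. That patient's T24 questionnaire is then completed 2 weeks after surgery. Under coding by allocation it still counts as an untreated score, contrary to the design assumption and to the definition of the control condition.

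Group III at T24 matters most. When group I reaches 24 weeks after surgery, group III is the only group scheduled to be still untreated, so its T24 score carries much of the primary contrast. The error could go either way: early relief in the control score would hide benefit, and early post-operative discomfort would exaggerate it.

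The two descriptions of assessment timing agree only when surgery is exactly on schedule. Off schedule, one keeps the questionnaire at its calendar week and the other moves it with the operation. Which one sites follow decides whether the problem can arise.

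**Working it through.** **Inputs from the article.** Sample size: SD 1.5, correlation 0.5 between repeated scores, target difference 1.0 point, 5% significance level (taken as two-sided), 95% power, 34 per arm, 38 after 10% loss. Primary analysis: a mixed model on scores at T0, T12, T24, T36 and T48, with 24 weeks after surgery against baseline as the main comparison.

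**Inputs assumed.** The article gives neither of these:
- *p*, the share of patients whose step-week score (the one due in the scheduled week of surgery) is taken after an early operation;
- *d*, the difference between that score and the true pre-operative score. Lower PAC-QOL is better, so a positive *d* means worse.

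**Step 1. Reproduce the planned size.** I used generalised least squares with equal correlation between visits, a separate mean for each visit and a separate effect for each lag since surgery. The step-week score is coded as pre-surgery. At 34 per arm the standard error of the 24-week effect is 0.276. Power is Φ(1.0/0.276 − 1.96) = 95.2%, and 34/0.9 rounds up to 38. The planned size is reproduced, so this model is a fair stand-in for the planned analysis.

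**Step 2. Weight of each step-week score in the 24-week estimate (correlation 0.5).**

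| Score | Weight |
|---|---|
| Group I at T0 | −0.50 |
| Group II at T12 | −0.37 |
| Group III at T24 | −0.70 |

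Groups II and III sum to −1.07, and all three to −1.57. At correlation 0.3 all three sum to −1.28.

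**Step 3. Bias.** If only the step-week scores are affected, bias = (sum of weights) × *p* × *d*. With *p* = 0.25 and *d* = ±0.5:
- groups II and III: 1.07 × 0.25 × 0.5 = 0.13 points;
- all three groups: 1.57 × 0.25 × 0.5 = 0.20 points;
- all three groups at correlation 0.3: 1.28 × 0.25 × 0.5 = 0.16 points.

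A positive *d* overstates benefit and a negative *d* understates it.

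**Step 4. Range.** Estimate of a true effect of −1.0 when groups II and III are affected, correlation 0.5 (power at 34 per arm in brackets where benefit is understated):

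| Early share *p* | *d* = −1.0 | *d* = −0.5 | *d* = +0.5 |
|---|---|---|---|
| 10% | −0.89 (90%) | −0.95 (93%) | −1.05 |
| 25% | −0.73 (76%) | −0.87 (88%) | −1.13 |
| 50% | −0.47 (39%) | −0.73 (76%) | −1.27 |

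**Step 5. Cost of setting such scores aside.** If a step-week score taken after surgery is not used as a control, the estimate stays at −1.0. Power falls from 95.2% to 94.6%, 93.3% and 89.8% for early shares of 10%, 25% and 50% in groups II and III. With group I also affected it is 94.3%, 92.4% and 87.3%.

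**The case against.** The strongest reply is that the harm needs three things at once: surgery before the visit, a visit held to the calendar, and exposure coded by allocation alone. The primary analysis section speaks only of scores before and after LVMR, and the endpoint names pre-surgery controls, so an analyst could code by the actual date of surgery. The visit schedule ties each operation to a numbered visit, so a moved operation might move the visit. This stands: contamination is possible under the stated rules but is not shown to happen.

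The Discussion warns that "availability of beds may represent a major bane for this trial", which points to late rather than early surgery. Late surgery leaves the step-week score truly pre-operative and only shortens the nominal 24 weeks, to about 22 at the edge of the window. Early surgery in group I would fall inside the 4-week run-in reserved for arranging the operation. Both points stand, and they make 0.13 a fairer illustration than 0.20.

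A reader might also infer that the modified intention-to-treat analysis contradicts a promised intention-to-treat analysis, or that off-window patients will be dropped or re-coded. The article does not support that. The withdrawal section concerns keeping data. The methods section does not say that the modified analysis replaces the one by allocation or removes anyone, and its definition may sit in the analysis plan, which is not shown.

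The reply does not remove the gap itself. The window and the by-allocation rule are set in the same paragraph, the calendar is fixed elsewhere, and the two descriptions of assessment timing diverge once surgery moves. An analysis plan written later cannot recover a pre-operative score due in that week if it was never taken.

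**Conclusion.** The point holds as a gap in the stated rules. Followed literally, they allow a score taken up to 2 weeks after surgery to serve as a control score in the primary contrast. It is not evidence that this has happened or will be common.

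The illustrative size is about 0.13 points in either direction, or about 0.20 if group I is also affected, against a target of 1.0. It rests on an assumed 25% early share and an assumed early difference of 0.5 points, and has no fixed sign. The planned sample size is not in error; it presumes clean control scores.

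The modified intention-to-treat analysis has an unclear standing relative to the analysis by allocation. That calls for a clarifying sentence and is not a contradiction.

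**What to change.** 1. State that the questionnaire due in the scheduled week of surgery is completed before the operation, and is brought forward if surgery is early.
2. State that no score taken after surgery is used as a pre-surgery control score. Where only a post-operative score exists, set it aside as a control value; the patient stays in the allocated group and all other scores are kept.
3. Reconcile Visit 2–8 with Ethical considerations, Specific, on whether assessments are counted from the run-in or from the operation.
4. State that the analysis of all randomised participants by allocation is primary and that the modified intention-to-treat analysis is supplementary.

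The cost is some protocol wording, an instruction to sites, and a small loss of precision where a step-week score has to be set aside: power of 93.3% instead of 95.2% if that applies to 25% of groups II and III.

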### Health economic outcomes

Within-trial stochastic analysis will compare the cost/success and cost/quality-adjusted life year (QALY) of LVMR. Patient-level cost-effectiveness will be analysed using standard bootstrapping methods to generate cost-effectiveness acceptability curves exploring value for money.

Cost-effectiveness models that extrapolate beyond 3–6 months duration are problematic in adult constipation, as subsequent care and outcomes are contingent upon subsequent care received and the underlying disease process. However, the CapaCiTY programme as a whole provides a unique opportunity to construct probabilistic models exploring optimal pathways from effectiveness and cost-effectiveness perspectives.

Since patients will (within the CapaCiTY programme) be followed along a pathway that includes a series of steps of care, it will be possible to construct costs and outcomes for a range of patient pathways providing comparative longer-term cost-effectiveness estimates. For example, it will be possible to ask whether INVEST or no-INVEST-led first-line care leads to lower overall costs or improved outcomes. Patient-level data from recruitment through the various work packages will be used to construct pragmatic, probabilistic models to explore optimal pathways from effectiveness and cost-effectiveness perspectives.

Analyses from NHS and societal perspectives will be supported by recording relevant resource use during each work package, and a common panel of outcomes. Adjustment for time preference will be at the socially accepted rate for cost-effectiveness analyses (currently 3.5% for costs and benefits).

### Qualitative interviews

Interviews will be digitally recorded, anonymised, transcribed verbatim and analysed using a pragmatic thematic analysis and NVivo8 software (QSR International Ltd, Warrington, UK) for data management. Data analysis will be developed as outlined by Fereday and Muir-Cochrane (1997) in the first instance by mapping key concepts derived from the transcripts (“charting”) and extracting emergent themes from the transcripts. Independent analyses will be conducted and resulting codes and themes will be compared and refined in discussion. Emergent themes, together with captured observational data, will form the basis of analytical interpretation.

## Ethical considerations

### General

The study will be carried out in accordance with the ethical principles in the Research Governance Framework for Health and Social Care, Second Edition, 2005 and its subsequent amendments and applicable legal and regulatory requirements.

CapaCiTY study 3 is the last of the three trials in the CapaCiTY Programme, all of which have been reviewed by the London – City and East REC. Within the programme, the three studies have separate protocols and patient information sheets to be consented separately as if they were distinct entities. This is necessary to limit patient information, which would otherwise be over-burdensome. We have discussed the use of sequential consent forms within one pragmatic enriched design with [name], national ethics advisor and Chair of the London – City and East REC, which confirms this will be practicable.

### Specific

The protocol has been reviewed by [name], Professor of Medical Ethics and Law at QMUL. Important considerations that have informed pragmatic design include:Wait-list controlled design: a waiting list control group serves the purpose of providing an untreated comparison for the active treatment group, while at the same time allowing the wait-listed participants an opportunity to obtain the intervention at a later date. In keeping with the basic ethical tenets of this design [99], the average wait will be shorter than that for routine services. This is achieved by randomising patients to receive urgent (4 weeks) or routine intervention as opposed to all having routine status as would be normal NHS clinical care. Current waiting times at most included centres are approximately 3–6 months for surgery, whereas the mean waiting time in the study will be 3 months. Survey evidence from 100 patients indicates that for a chronic condition such as CC, patients are prepared to accept a randomization strategy that allocates them to a one in three chance of waiting up to 24 weeks for surgical treatment;Limitation of intimate examinations to one time point (not repeated if performed before recruitment);Timings of outcomes: within the standardised outcome framework, outcomes will be undertaken at fixed intervals of 12 weeks before and after the intervention to 48 weeks follow up within the stepped-wedge study and thereafter in 12-week intervals within the cohort assessments up to 72 weeks. For a period of 24 weeks of follow up post-surgery, patients will not progress to further therapies, thus preventing outcome “contamination”. This “quarantine” period from major therapy progression is required to give a reasonable clinical impression of outcome. This delay is akin to that in usual NHS care during which general supportive care will be provided while further interventions are considered. Thus, this proposed “quarantine” period to 6 months confers no disadvantage and may even represent an acceleration of treatment progression. Ethically, this is viewed as a reasonable trade-off for the commitment to the research programme;Recruitment and consent: study 3 represents one of the three studies incorporated in the NIHR-funded CapaCiTY programme. Although patients may have moved sequentially through earlier treatments (and therefore studies) during the programme course, study 3 will be consented as a distinct single entity.

## Safety considerations

### Surgery

LVMR has a number of established specific complications in addition to the general risks of surgery. Data on these complications are in the public domain [72] and can be considered to be expected events. These will, however, still be recorded for outcome reporting.

#### Intra-operative complications

Intra-operative complications include inadvertent injury to other intraperitoneal viscera. These are common to all types of laparoscopic surgery, such as:Bowel, ureter, bladder or vaginal injuries or perforationsVascular or nerve damage

#### Post-operative complications

Urinary retention (<10%)Urinary tract infectionWorsening of, or *de novo* urinary incontinencePort site complications (early or late port site hernia; bleeding or wound infection)Pelvic sepsisPelvic painHaemorrhage especially from the posterior vaginal wallVaginal or rectal perforationFaecal impaction (rare)Small bowel obstructionSexual dysfunction (rare)Dyspareunia (uncommon) – usually resolves with time [100]Osteomyelitis of the sacrum and spondylodiscitis [101]Venous thromboembolism

#### Prosthesis-related complications

Minor mesh complicationsMesh infection (<3%)Mesh erosion (<3%)Mesh sinus

Minor mesh complications can be managed by local measures including suture sinus removal, mesh trimming, performed endo-rectally or endo-vaginally with subsequent healing. Major mesh complications include (1) generalised mesh sepsis requiring mesh removal endo-rectally or trans-abdominally or both, with or without partial or complete rectal excision and (2) rectovaginal fistula also requiring mesh removal endo-rectally or trans-abdominally or both +/-partial or complete rectal excision.

